## Abstract

**Background:**

Whilst women with diabetes are at risk of having a pregnancy complicated by foetal macrosomia, a small but important minority of women develop placental dysfunction leading to a small for gestational age infant (SGA < 10th centile) (20%) and/or the development of pre-eclampsia (12–18%) which may in some cases require preterm birth. In the UK, currently, metformin is offered as first line to treat diabetes during pregnancy, regardless of the risk of placental disease; however, the effect of metformin on placental function and foetal growth remains unclear. Metformin Impact on Maternal and Infant Cardiometabolic Health (MIMICH) and Metformin Impact on Maternal and Infant Cardiometabolic Health After Pregnancy (MIMICH II) aim to better understand the impact of metformin in the context of pregnancies at high risk of placental disease by evaluating the effect of metformin on foetal growth, placental function and maternal and infant cardiometabolic health.

**Methods:**

MIMICH is a randomised control trial (RCT) comparing routine treatment for diabetes, the standard of care, to withholding metformin (the intervention) during pregnancy, in women with type 2 diabetes or gestational diabetes (GDM) who have maternal or uteroplacental risk factors for placental disease in a target sample of 225 participants. Participants receive the recommended schedule of antenatal care, including serial biometry ultrasound with the addition of fractional thigh volume measurement. The primary outcome will be change in estimated weight z-score from second trimester to birth. The MIMICH II study will follow up the mothers and infants at 3–6 months and 12–15 months after pregnancy. Study procedures include anthropometric measurements from both mother and baby, data collection about medications, complications after birth and feeding, and maternal blood sampling. Infant echocardiography, blood pressure measurements and venepuncture will also be undertaken where possible.

**Discussion:**

Previous studies investigating hypoglycaemic agents in pregnancy have used birthweight as the primary outcome. In pregnancies where there are conflicting exposures influencing foetal growth and placental function (e.g. hypertension and hyperglycaemia), absolute birthweight is not sufficient to detect subtle, but clinically significant changes in foetal growth and placental function. To address this limitation, longitudinal measures of foetal growth will be used to quantify the deviation in foetal growth trajectory in the third trimester, using comparison with foetal growth prediction based on second trimester biometry from the same foetus.

**Trial registration:**

ISRCTN13866189. Registered on February 15, 2021.

**Supplementary Information:**

The online version contains supplementary material available at 10.1186/s13063-025-09154-5.

## Introduction

### Background {6a}

Amongst women* with poor cardiometabolic health embarking on pregnancy, hyperglycaemia is a very common feature. The prevalence of hyperglycaemia is increasing across Europe, alongside increasing rates of older maternal age, obesity and hypertension. Gestational diabetes (GDM) rates have recently been estimated at 5.4% (3.8–7.8) [1] and the prevalence of type 2 diabetes has doubled (0.5–1.1% between 2008 and 2012) [2]. As a result of the fact that the majority of women with hyperglycaemia have other cardiometabolic risk factors (family history, obesity, dyslipidaemia, hypertension), compared to healthy subjects these women have a three- to fourfold increased risk of pregnancy hypertension (7.4%) [3]. Rates of pre-eclampsia in women with type 2 diabetes have been reported to be as high as 31% [4] and women with a combination of diabetes and vascular disease are six times more likely to develop foetal growth restriction (FGR) [5].

Birth weight is a well-established factor for adult cardiometabolic disease. The short- and long-term impacts of prematurity and growth restriction for infants are much greater than of macrosomia [6]. Whilst foetal macrosomia is the common pathology in women with hyperglycaemia, an important minority (~ 3%) [5] will conversely develop severe placental disease leading to FGR requiring early preterm delivery to prevent stillbirth [7]. An additional 20% will have a small for gestational age (SGA, < 10th centile) baby and 12–18% will develop pre-eclampsia [3, 5].

*Throughout the protocol, in our references to women, we also encompass birthing people within this context.

#### Background: antenatal influence of metformin

Current practice in the UK is to offer metformin to all women with hyperglycaemia irrespective of potential risk factors for placental disease [8, 9], but the effect of metformin on placental function and foetal growth remains uncertain [10]. A recent Canadian RCT of women with type 2 diabetes demonstrated increased rates of SGA in women treated with metformin [11]. Another recent RCT comparing metformin and insulin in Spain found no difference in growth as a secondary outcome [12], and a meta-analysis of RCTs in 2024 found no difference in SGA rates between metformin and insulin treatment [13]. Notably, however, these studies are not looking primarily at growth restriction and do not consider the sub-set of patients with risk of placental dysfunction. In an animal model, metformin has been shown to accumulate in the foetus, demonstrated at delivery, and is linked to growth restriction [14].

The effect of metformin on cellular metabolism has not been fully explained and remains controversial; metformin has been shown to disrupt mitochondrial respiration [15, 16], alter redox status [17], impair tumour growth [18] and cellular proliferation under hypoxic and nutrient deficient conditions [19]. All of these actions suggest that metformin could negatively affect placental function particularly in the context of oxidative stress and hypoxia, although this has not been tested directly. Conversely, metformin has been demonstrated to have significant anti-inflammatory properties in the systemic vasculature [20, 21] and in trophoblast cell lines [22]. There is some circumstantial evidence from the clinical trials, which have used metformin to limit foetal growth in women with hyperglycaemia, that metformin reduces the risk of gestational hypertension [23, 24]. However, the effect on the rate of pre-eclampsia was not clear [25]. Meta-analysis by Wu et al. [13] showed no difference in gestational hypertension between metformin and insulin, but less pre-eclampsia in metformin treatment. Disagreement in the literature about these may reflect different disease aetiologies between some types of pre-eclampsia and gestational hypertension. The potential relationship between metformin and hypertensive disease is further highlighted by the finding that hypertensive disease correlates with the need for insulin treatment and metformin monotherapy failure [26]. The effect of metformin on both maternal cardiometabolic health and placental function therefore warrants further investigation so that this therapy can be targeted to the women who will benefit most [10].

#### Background: postnatal influence of metformin (MIMICH II)

To date, there is only limited evidence regarding the impact of in utero metformin exposure on childhood metabolic health. Mouse studies investigating prenatal exposure to metformin have reported opposing effects on glucose tolerance and insulin sensitivity. In a study by Gregg et al. [27], improved glucose tolerance was demonstrated in male offspring exposed to metformin in utero. In contrast, in a study by Salomäki et al. [28], metformin-exposed offspring were lighter at birth but demonstrated excessive weight gain and impaired glucose tolerance when fed a high-fat diet after weaning. The limited available human studies have demonstrated that children exposed to metformin in utero are heavier at 12 months [29], taller and heavier at 18 months [30] and have increased subcutaneous fat deposition at the age of 2 (Metformin in GDM (MIG) Trial) [31]. Children from the MIG trial have now been followed up to age 7 (Adelaide) and 9 (Auckland) [32]. Whilst there were no significant differences in the age 7 children from Adelaide, the children from Auckland aged 9 were slightly larger measured by weight, arm/waist circumferences and waist:height ratio (*p* < 0.05). A recent meta-analysis has synthesised the available childhood follow-up data and from pregnancy studies where metformin was prescribed to women with polycystic ovarian syndrome (PCOS) and uncomplicated GDM (338 children exposed to metformin and 346 not exposed) [33]. Overall, metformin-exposed children were heavier than controls (standard mean difference 0.26 [0.11–0.41], *p* = 0.0008) at 2 years.

The MiTy trial, which showed an association with SGA in the metformin-treated group, recently published data about the infants of these mothers at 2 years and found their anthropometric measures were similar between groups at the 2-year endpoint, but that metformin-exposed male infants had a different growth trajectory, and that BMI was higher from 6 to 24 months [34]. Postnatal catch-up or accelerated growth often defined as a delta weight SD score > 0.5 or 0.67 has been consistently associated with insulin resistance and metabolic syndrome-related disorders (e.g. type 2 diabetes) in later life [35–37]. Accelerated growth during early postnatal life, irrespective of birth weight, has been shown to associate with changes in β-cell function at 12 months [38, 39] and appears to be particularly important for metabolic health in later life [40]. It is unclear from existing studies whether metformin exposure in utero affects postnatal catch-up and therefore impacts future cardiometabolic health in later life. Of note, infants exposed to metformin in the EMPOWaR study [41], a randomised study of obese pregnant women, were thinner (lower ponderal index) at birth, which, if associated with accelerated postnatal weight gain (akin to the mouse studies), could confer an increased cardiometabolic risk to the offspring [42].

#### Rationale

Given the uncertainty regarding the potential benefits (improvement in maternal metabolic health and reduction in hypertensive disease), but potential negative effects on placental function (reduction in foetal growth and antiproliferative cellular actions), highlighted above and by a recent expert review [10], a trial of metformin in women with hyperglycaemia and risk factors for placental disease is justified. In addition, it is essential that effects on offspring are also investigated, and doing so in this population allows for antenatal foetal growth trajectory and postnatal infant growth trajectory to be connected.

As it is routine clinical practice to offer metformin to women with hyperglycaemia, the intervention in this study will be to withhold metformin and manage hyperglycaemia with diet/insulin alone. A randomised study is essential to avoid treatment-selection bias, and the study is open-label to aid the ongoing management of diabetes. No previous studies have investigated the effect of metformin on placental function, foetal growth and maternal cardiometabolic health in women with hyperglycaemia and concurrent risk factors for placental disease. This study is made possible through access to a large population of high-risk pregnancies across Manchester (3 hospital sites serving 18,000 births per year) and the specialist translational clinic infrastructure which incorporates 3D volumetric ultrasound foetal growth assessment.

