### Trial design {8}

MIMICH is a phase III, two-arm, single-centre, open-label pragmatic randomised controlled trial (RCT). The study framework aims to assess the superiority of withholding metformin in otherwise standard pregnancy diabetes care, determined by foetal growth trajectory and placental function. Randomisation will take place in a 1:1 ratio. Following the RCT, participants who provide consent will be enrolled in an observational cohort study assessing postnatal maternal and infant cardiometabolic health, with follow-up visits at 3–6 months and again at 12–48 months postpartum.

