### Outcomes {12}

#### MIMICH

Outcomes will be recorded in the electronic case report form, hosted on REDCap. Outcomes will be collected from baseline to maternal discharge post-birth. Neonatal outcomes will be recorded up to 28 days after birth.

Primary outcome:

Third trimester foetal growth velocity, assessed by change in foetal growth z-score between 20 and 29 weeks’ gestation (average) and birth.

At each scan, the estimated foetal weight (EFW) in grams will be calculated using 2D biometry and fractional thigh volume (TVol) measurements using a standard formula [44] and converted to a z-score [43]. The delta change in z-score between the average z-score of scans performed between 20 and 29 weeks and the birthweight z-score will be calculated.

Secondary outcomes:

During pregnancy, secondary outcomes will be reported as per standard for pregnancy intervention trials. Secondary foetal growth and birthweight analyses will be assessed according to treatment group in line with the primary outcome analysis. Outcomes relating to blood glucose control (as an indicator of treatment effect) will similarly be compared between groups, as will blood pressure and hypertensive complications. Reporting and analysis of secondary outcomes will be described in full in the statistical analysis plan; to avoid issues of multiple testing, not all secondary outcomes will be compared between treatment groups. Secondary outcomes will be assessed using adjusted linear regression for continuous outcomes and chi-squared for categorical outcomes; *p* values > 0.01 and < 0.05 will be interpreted with caution. Where appropriate, outcomes will be presented with a treatment effect and confidence intervals; other outcomes will be presented with summary statistics only.

Prespecified secondary outcomes:

Adherence/acceptability:Number of missed doses—calculated as an average over pregnancy from the number of missed doses reported in the 7 days prior to each study visit (adjusted for number of study visits)Number of women unable to comply with allocated treatment (cross over)Undesirable effects of allocated treatment (number of women reporting undesirable effects associated with metformin and/or insulin/number of women receiving metformin or insulin treatment)Treatment satisfaction with allocated medication regime (questionnaire)Acceptability of allocated medication regime (questionnaire)

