#### Outcomes for MIMICH II

Primary infant outcome: Difference in the delta (birth to visit 2) weight SD score between infants following maternal treatment with or without metformin

Infant secondary outcomes:Metabolic health indices including biochemical (insulin, glucose, lipid profile, leptin, adiponectin)Anthropometric measurements (crown-rump, crown-heel lengths; weight; arm, thigh, head, abdominal circumferences; biceps, triceps, subscapular skinfold thicknesses) expressed as z-scores using WHO charts where applicableCardiac measurements including systolic and diastolic blood pressure and echocardiogram (left ventricular dimensions, diastolic function and systolic function)Transcriptomics and metabolomics are collected from infant and mother and differentially expressed genes and metabolites will be determined between metformin-exposed and non-exposed infants

Maternal secondary outcomes: Postnatal weight change (from booking to late pregnancy), adiposity (waist:hip ratio, biceps, triceps, subscapular skinfold thicknesses), cardiometabolic health measurements (insulin resistance, lipids, hsCRP, inflammatory cytokines, BP)

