### Sample size considerations {14}

The primary outcome is a change in foetal growth velocity in the third trimester. Our group has pioneered the use of volumetric ultrasound techniques to improve the detection of foetal growth abnormalities [47, 48]. Previous studies investigating hypoglycaemic agents in pregnancy have used birthweight as the primary outcome, which provides only a crude estimate of foetal growth. In pregnancies where there are conflicting exposures influencing foetal growth and placental function (e.g. hypertension and hyperglycaemia), absolute birthweight is not sufficient to detect subtle, but clinically significant changes in foetal growth and placental function. To address this limitation, in this study, longitudinal measures of foetal growth will be used to quantify the deviation in foetal growth in the third trimester. This will be derived from the delta z-score in estimated foetal weight (using the modified EFW TVol formula [44]) over the third trimester using WHO foetal growth charts [43]. This will provide a more sensitive assessment of the effect of metformin on foetal growth than birthweight alone; the use of a continuous measure as a primary outcome also makes the study more efficient as it requires a smaller sample size. In order to verify the primary outcome, the eCRF will capture the TVol measurement and the EFW at each scan as well as recording the 2nd trimester and 3rd trimester deviation scores. The source data (scan report) will verify the 2D biometry.

In a comparison of women with type 2 diabetes treated with metformin recruited to the VELOCITY study, the mean delta z-score between the second trimester and birth was − 0.51 (SD 1.1) for women with a placental disease risk factor (*n* = 34) and 0.30 (SD 0.9) in women without a risk factor (*n* = 45). A sample size of 190 women (95 in each group) will provide 80% power to detect a clinically significant difference in delta z-scores of 0.41 (SD 1.0) between the treatment groups; this difference would reflect a rightward shift in the birthweight distribution in women in whom metformin was withheld to a mean of − 0.1.

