An adjusted analysis of the effect of the intervention (withholding metformin) on foetal growth will include covariates (mean daily glucose, time in target) which are known to influence foetal growth to improve the precision of the treatment effect as appropriate. Change in foetal weight z-score provides a continuous measure of late pregnancy growth trajectory derived from early foetal biometry and 3D volumetric measurements and therefore the foetus is its own control. Importantly, this removes the need to adjust for infant sex. Furthermore, as the measurement of foetal weight z-scores using 3D foetal thigh volumes, and therefore calculation of delta z-scores is done after birth, the risk of bias is minimised. In the MiTy trial [11], a comparison of metformin vs no metformin in unselected women with type 2 diabetes, the difference in birthweight z-score was − 0.28 (− 0.45 to − 0.10).

Recruitment figures have been based on attendances to the Manchester Antenatal Vascular Service (MAViS) clinic, which provides care for women with cardiometabolic disease, and the diabetes service across Manchester Foundation Trust. Allowing for the fact that the proposed study will draw from a population of 16,500 pregnancies per annum, eligible women will include those with type 2 diabetes (*n* ≈ 108) and women who develop GDM with additional risk factors for placental disease (*n* ≈ 420). A recruitment rate of 50% would yield an available cohort of approximately 225 women (10% dropout) over a 36-month time frame. Based on figures from the MAViS cohort, 20% would be expected to develop a small for gestational age (SGA < 10th centile) and 12–18% pre-eclampsia.

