### Methods for additional analyses (e.g. subgroup analyses) {20b}

Planned subgroup analyses on the primary outcome will investigate interactions between treatment effects and minimisation factors, with separate estimates and CIs reported for these subgroups of participants. In order to explore potential mechanism of action, exploratory analyses will estimate the effect of treatment received on the foetal growth outcomes.

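### Withholding metformin means stopping for some women and not starting for others, and metformin use at randomisation is not a named minimisation factor, covariate or subgroup

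*Protocol article*

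**What the plan says.** All references are to the protocol article.

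- **Intervention (Rationale).** Because metformin is routinely offered, "the intervention in this study will be to withhold metformin and manage hyperglycaemia with diet/insulin alone".
- **Who may enter (Eligibility criteria {10}).** Women from 6+0 to 30+0 weeks with pre-pregnancy type 2 diabetes, diabetes found before 24 weeks, or GDM found later. The only exclusion naming metformin is a medical contraindication. There is no rule on current or earlier use.
- **Routine use.** The section on the antenatal influence of metformin says UK practice is to offer it to all women with hyperglycaemia. Intervention description {11a} adds that it is started when diet and lifestyle measures do not reach the glucose targets.
- **Baseline data (Table 1).** Medication, metformin dose and missed doses are recorded at the baseline visit.
- **Minimisation {16a}.** Diabetes diagnosed before or after 24 weeks, type of placental risk factor, and three bands of gestational age.
- **Primary model {20a}.** Adjusted for the starting z-score and the minimisation factors, subject to confirmation in the SAP.
- **Subgroups {20b}.** "Planned subgroup analyses on the primary outcome will investigate interactions between treatment effects and minimisation factors". An exploratory analysis by treatment received is also planned for foetal growth.
- **MIMICH II outcomes.** For the omics outcomes, "differentially expressed genes and metabolites will be determined between metformin-exposed and non-exposed infants". The MIMICH II part of the sample size section uses the same two labels for the weight comparison.

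**The concern.** For a woman already on metformin, allocation to the intervention arm means stopping it. For a woman who has not begun, it means not starting. These are different contrasts in foetal exposure, and the primary estimate mixes them.

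The endpoint makes the difference concrete. It is the birthweight z-score minus the average z-score from scans at 20 to 29 weeks. For a current user who enters near 30 weeks, the starting value was measured on metformin in both arms, so the change reflects stopping versus continuing. For a metformin-naive woman who enters equally late, the starting value was unexposed in both arms, so the change reflects not starting versus having metformin available.

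The Discussion says the trial should inform guidance on metformin in this group. Whether to start and whether to stop are separate guidance questions. Metformin use at entry is also plausibly prognostic for growth, since it marks both the severity of diabetes and earlier exposure. Leaving it out of the model would forgo some precision and leave a chance imbalance only partly corrected.

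In MIMICH II, an infant in the withheld arm may have been exposed before randomisation, so a non-exposed label would not fit every infant in that arm.

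**Working it through.** **1. Do the planned factors separate users from non-users?**

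| Factor | What it tells us about metformin use at entry |
|---|---|
| Diagnosis before 24 weeks | Pools pre-pregnancy type 2 diabetes (likeliest long-term users) with newly diagnosed women, who may or may not have started |
| Diagnosis after 24 weeks | At most about 30 − 24 = 6 weeks of treatment before entry |
| Gestational age at entry | Limits the length of earlier exposure, but does not show whether there was any |
| Type of placental risk factor | No direct information |

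A woman diagnosed at 20 weeks and randomised at 28 falls in the same cell whether or not she takes metformin. The separation is partial.

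**2. The plan's own sample size.** "A sample size of 190 women (95 in each group) will provide 80% power" for a "clinically significant difference in delta z-scores of 0.41 (SD 1.0) between the treatment groups". No alpha is stated for the primary outcome; I assume two-sided 0.05.

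- n per arm = 2 × (1.96 + 0.84)² × 1.0² / 0.41² = 15.68 / 0.1681 = 93.3, so 94 (95 with the t-test).
- Power at 95 per arm: 0.41 / √(2/95) = 2.83; 2.83 − 1.96 = 0.87; power about 81% (80% by t-test).
- One-sided 0.05 would need only 74 per arm, so two-sided fits.

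The stated figure reproduces, and this point does not change it.

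**3. Size of the mix.** From the eligible pool in the sample size section: 108 / (108 + 420) = 108/528 = 20.5% have type 2 diabetes. This is not the share on metformin, which the article does not give. It could be lower (some women with type 2 diabetes not taking it) or higher (other women already started).

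**4. Illustration of dilution; f and r are assumptions.** Let a share f be users at entry, with effect r × 0.41, and let the rest have effect 0.41. The average effect is 0.41 × (1 − f(1 − r)).

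| f | r | Average effect | Power at 95 per arm | n per arm for 80% |
|---|---|---|---|---|
| 10% | 0.5 | 0.389 | 77% | 104 |
| 20.5% | 0.75 | 0.389 | 77% | 104 |
| 20.5% | 0.5 | 0.368 | 72% | 116 |
| 20.5% | 0 | 0.326 | 61% | 148 |
| 40% | 0.5 | 0.328 | 62% | 146 |

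The article does not say whether r is below or above 1. If stopping had the larger effect, the average would exceed 0.41.

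**5. Precision of the proposed interaction.** Take f = 20.5%, 190 women and SD 1.0: 190 × 0.205 ≈ 39 users and 151 non-users, split equally by arm.

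- SE of the effect in users: √(4/39) = 0.32. In non-users: √(4/151) = 0.16.
- SE of the interaction: √(4/39 + 4/151) = √0.129 = 0.36. The 95% half-width is 1.96 × 0.36 ≈ 0.70.
- Difference detectable with 80% power: 2.80 × 0.36 ≈ 1.0 z-score.

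The interaction can therefore be only exploratory.

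**The case against.** The strongest defence has five parts.

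- **The covariates are not final.** The article leaves confirmation of the model to the SAP, which is not shown. This stands: one cannot say the analysis will not adjust for metformin use, only that it is not among the named factors. The minimisation list is fixed here, and the stated subgroups are tied to it.
- **Proxies are in place.** Time of diagnosis and gestational age are minimised, named for the model and tested for interaction. This stands in part: they reduce the problem without removing it.
- **A pragmatic trial may average over entry states.** The objective is the effect of withholding, and randomisation protects that comparison. A reader might infer that the primary result is biased or confounded by earlier use. The documents do not support that; any imbalance would be due to chance.
- **The endpoint concerns late pregnancy.** Each foetus serves as its own control, so earlier exposure is partly absorbed by the starting z-score. That is fair, but the starting value itself is measured under different exposure in users and non-users.
- **The MIMICH II labels are not defined.** The primary infant outcome is worded by maternal treatment, and nowhere does the article equate non-exposed with the withheld arm. A reader might infer that exposed infants will be misclassified. The article shows only that the label is ambiguous.

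**Conclusion.** The point holds as one of interpretation and precision. Eligibility admits both current users and women not on metformin. The plan names no variable that distinguishes them directly, and its proxies separate them only partly. The intention-to-treat estimate remains a valid average effect of the withholding strategy, but the weights on stopping and not starting are unknown. The only related figure is the 20.5% share with type 2 diabetes.

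Two stronger readings should be resisted. First, the trial is not shown to be underpowered: powers of 61% to 77% follow only from assumed values of f and r, and the direction of any difference is unknown. Second, very long earlier exposure is not shown to be typical. Metformin from conception to entry at 30+0 would cover 30 of an assumed 38 to 40 weeks (75% to 79%), but that is an upper bound for one kind of participant and describes the whole pregnancy, not the growth window of the primary outcome.

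**What to change.** Before the analysis, and without changing eligibility, treatment or minimisation:

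1. Define metformin use at randomisation (yes/no) from the medication and metformin dose recorded at the baseline visit, and report it by arm.
2. Add it as a covariate in the primary model.
3. Add it to the planned subgroup list as a prespecified exploratory treatment interaction, with an estimate and confidence interval for women who were taking metformin and for those who were not.
4. In MIMICH II, describe the randomised comparison by allocated arm, not as exposed versus non-exposed, and report metformin exposure before randomisation from the available records.

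The cost is SAP wording and one or two degrees of freedom. The yes/no variable should need no new data; weeks of earlier exposure may require start dates from case notes. The interaction will be imprecise, so the two estimates should be read for size and interval, not for significance.
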